#### Data Analysis

Inferential statistics help researchers draw conclusions about populations based on sample data, providing insights into social phenomena [153]. Machine learning, as a subset of artificial intelligence (AI) techniques, analyzes large datasets to identify patterns and make predictions [154]. These methods are transformative in gender studies, uncovering patterns in gender-related data and deepening the understanding of social inequalities and biases [155]. These methods have been successfully applied to areas such as forecasting gender-based violence, further demonstrating their relevance in social sciences [156].

Exploratory data analysis (EDA) will be crucial in examining CP and its connection to past or current IPV against women. EDA uses techniques such as scatterplots, clustering algorithms, and principal component analysis to investigate multidimensional datasets [157]. Scatterplots help identify correlations between sociodemographic variables, clustering algorithms reveal subgroups within the population, and principal component analysis reduces dimensionality to uncover latent factors such as the relationship between gender identity and social support [158]. The use of EDA will allow us to detect groups and subgroups at a glance by creating subclusters, that is, more specific profiles in each of the groups.

Inferential statistical methods will be applied to differentiate between women with CP alone and those with CP who have experienced IPV in the past or are currently experiencing IPV. Hypothesis testing, estimation, and prediction techniques will be used to make comparisons, with visual tools such as boxplots for examining variable distributions across groups. We will use 2-tailed *t* tests and ANOVA to compare means across groups [159].

Feature ranking techniques will help identify the most relevant variables for accurate classification. Methods such as information gain, gain ratio, Gini index, and relief will determine the importance of features such as education, socioeconomic status, pain level, and social support [160]. This feature ranking will help prioritize the most influential factors affecting each group, including those based on country distribution.

Machine learning classifiers, including random forest, decision trees, adaptive boosting, gradient boosting, and support vector machines, will be applied to classify data. The process will involve training, validation, and testing phases, with hyperparameter tuning during validation. K-fold cross-validation will be used to evaluate the model’s performance, using training, validation, and testing phases across different folds [161]. The model’s performance will be assessed using metrics such as precision, recall, *F*_1_-score, and receiver operating characteristic curves [162].

Feature importance evaluation will identify which variables most significantly influence the model’s predictions. This analysis, combined with explanatory models such as Shapley additive explanations, will provide further insights into how features impact classification outcomes [163]. These methods are widely used in gender studies to uncover social patterns and inequalities. By combining Shapley additive explanations values with EDA, we aim to pinpoint the most significant factors that explain different profiles in the data [164].

Data analysis will be conducted using Python (Python Software Foundation), with libraries such as *pandas* (for data manipulation), *NumPy* (for numerical operations), *scikit-learn* (for machine learning), and the combination of *matplotlib* and *seaborn* (for visualization). This suite of tools provides an efficient framework for inferential statistical analysis and exploratory data. Comparable analysis could also be performed using R (R Foundation for Statistical Computing), which presents similar usability for data study. R comes with *tidyverse*—a package that merges *dplyr* and *ggplot2* for visualizing data—and *caret* for building predictive models. Similar software such as MATLAB (The MathWorks, Inc) also allows for wider functionality for statistical computing and algorithm development.

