For the quantitative phase (phase 2), participants will fill in anonymous web-based questionnaires, as outlined in the informed consent form. For security reasons, participants must complete the questionnaire at the center they attend. Allowing them to complete it at home could put them at risk because their aggressors could see their responses. Participants will submit their informed consent to a designated professional at the relevant health center, unit, or association. This professional will have a list of codes. They will have to assign one to each participant (unknown to them) and will have to enter it so that each participant can start or pick up the questionnaire where they left off the last time. The professional will collect all informed consent forms and submit them to the principal investigator in a sealed envelope. Throughout the study, the research team will not have access to any personal identifying information.

In both studies, the web-based closed questionnaires will be designed using LimeSurvey, a private platform that meets security standards and data protection regulations. The responses will be stored in a database under the supervision of one of the collaborating universities. Before commencing the studies, the questionnaires will be piloted with a sample of 10 women to address any issues related to content, usability, or technical functionality of the web-based platform.

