#### Sample Size Calculation

To calculate the sample size, the prevalence of the pain-avoidance activity pattern was used, which is typically present in cases of highly disabling CP [102]. Specifically, we considered several factors: first, the expected prevalence ratio assumed to be 2.0 between individuals with CP who are exposed to IPV against women and those who are not. Second, we estimated the prevalence of the pain-avoidance activity pattern within the study population, assuming it to be approximately 20%. While a previous study found that 40.4% of patients with fibromyalgia exhibited this pattern [133], we decided to use a more conservative estimate, given that the prevalence of this behavior is likely lower among the broader population of patients with CP. Finally, we accounted for the expected prevalence of IPV exposure among women with CP, estimated at 30% based on findings from earlier research [23].

We have defined the risk level α as 5% and the study power as 90%. The program used for size calculation was a macro, !NSize, for SPSS Statistics [134]. On the basis of these parameters, the required sample size consists of 359 women with CP: 193 (53.8%) with CP alone, 83 (23.1%) with CP and a current history of IPV, and 83 (23.1%) with CP and a past history of IPV.

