### Access to the Study

Participants will have to indicate how they accessed the study (associations and support centers for IPV against women, CP associations, CP units, or primary health care centers).

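### Phase 2 women are recruited and answer within centers partly defined by IPV, but the stated tests and the 359-woman calculation treat them as independent, and no center variable is listed

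*Protocol article*

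**What the plan says.** Phase 2 uses the phase 1 channels: IPV associations and support centers, CP associations, CP units and primary health care centers. Directors pass on the link, and center professionals enter a code and activate the survey. Under Ethical Considerations, "participants must complete the questionnaire at the center they attend".

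Under Access to the Study, "Participants will have to indicate how they accessed the study"; the options are the types of channel. Table 2 marks this variable for control purposes and not for data analysis. No center variable is listed.

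For the group comparisons, the phase 2 Data Analysis section says "We will use 2-tailed *t* tests and ANOVA to compare means across groups". For the classifiers it names k-fold cross-validation with "training, validation, and testing phases across different folds", without saying how women are assigned to folds.

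Under Sample Size Calculation, "the required sample size consists of 359 women with CP", split 193, 83 and 83. The Limitations section mentions nonprobability sampling but not clustering.

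**The concern.** Women at one center share staff, services, catchment area and answering conditions. Some outcomes, such as prescribed analgesics and general practitioner visits, depend partly on local practice. Some within-center correlation is therefore plausible.

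Correlation alone would not distort a comparison made within centers. It does when the groups sit in different centers, because between-center variation then enters the group difference while the t test and ANOVA standard errors leave it out. The design points that way. The CP-alone group must never have experienced IPV or any other violence, so an IPV support center can hardly supply it, whereas it is an obvious source for the 166 IPV women (83 + 83).

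Two things are at stake. One is the error rate of the group comparisons. The other is whether classifier performance carries over to new centers, which matters because the findings are meant to help detect IPV in health care settings and to inform guidelines.

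Timing matters too. Records are anonymous, so if center is not captured at entry, no later plan can fit a center effect, group the folds or estimate the ICC.

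**Working it through.** **1. The plan's own figure.** Inputs from Sample Size Calculation: "the expected prevalence ratio assumed to be 2.0 between individuals with CP who are exposed to IPV"; prevalence of pain avoidance, "assuming it to be approximately 20" per cent; IPV exposure 30%; and "We have defined the risk level α as 5% and the study power as 90" per cent. Take 0.20 as the rate in unexposed women and 0.40 in exposed, with allocation r = 3/7.

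- Pooled rate: (0.20 + 3/7 × 0.40) / (1 + 3/7) = 0.26.
- n₀ = [1.96√(0.26 × 0.74 × (1 + 7/3)) + 1.2816√(0.20 × 0.80 + 0.40 × 0.60 × 7/3)]² / 0.20² = 176.5.
- Continuity correction: (n₀/4)[1 + √(1 + 2(1 + r)/(r n₀ × 0.20))]² = 192.8, so 193 unexposed; 192.8 × 3/7 = 82.6, so 83 exposed.
- 193 + 83 = 276; a second IPV group of 83 gives 359.

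The stated figure reproduces exactly from a formula for independent women, with no design effect.

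**2. Limiting case: IPV status fully fixed by center.** Design effect DE = 1 + (m − 1) × ICC, with m women per center. Actual two-sided α of a nominal 5% test = 2[1 − Φ(1.96/√DE)]. Both m and the ICC are assumptions.

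| m | ICC | DE | 359 × DE | actual α |
|---|---|---|---|---|
| 10 | 0.01 | 1.09 | 392 | 6.0% |
| 10 | 0.05 | 1.45 | 521 | 10.4% |
| 10 | 0.10 | 1.90 | 683 | 15.5% |
| 20 | 0.01 | 1.19 | 428 | 7.2% |
| 20 | 0.05 | 1.95 | 701 | 16.0% |
| 20 | 0.10 | 2.90 | 1042 | 25.0% |

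**3. Partial alignment, by simulation.** Score = center effect (variance = ICC) + individual error (total variance 1), with no true group difference and groups of 193/83/83. One third of centers are IPV centers, and a set share of IPV women comes from them. All of these layout inputs are assumed. Rejection rate of the ordinary t test, CP alone against any IPV:

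| Assumptions | t-test type I error |
|---|---|
| ICC 0.05, 60%–100% aligned, 12 centers | about 12%–22% |
| same, 20 centers | about 10%–18% |
| same, 30 centers | about 8%–12% |
| ICC 0.05, 30% aligned, 12–30 centers | about 6%–7% |
| ICC 0.01, most layouts | about 5%–7% |
| ICC 0.01, 12 centers, fully aligned | up to about 10% |
| no alignment | about 5% |

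Separate runs agree to within about three percentage points; the 30-center row, for instance, came out at 7%–15% in another run. At ICC 0.05 and 60%–100% alignment, the three-group ANOVA gave 11%–19% (12 centers), 9%–14% (20) and 6%–12% (30).

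A different layout (35% of centers with 95% IPV women, the rest with 20%) gave t-test error at ICC 0.05 of 13.6% (12 centers), 10.1% (18) and 7.4% (36). At ICC 0.01 with 36 centers it was 5.2%.

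**4. Classifier.** In that second layout, a ridge linear classifier was fitted to 30 predictors unrelated to IPV, at ICC 0.05. Random 5-fold validation gave a mean AUC of 0.58 (12 centers), 0.55 (18) and 0.53 (36). With folds grouped by center the AUC was 0.49–0.50. Without alignment both schemes stayed near 0.50. Center need not be a listed feature: center-level shifts in the listed scales are enough.

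**The case against.** The size rests on inputs the article does not give. It states no ICC, number of centers or women per center, and nothing on the share of IPV women who will come from IPV centers. The CP channels could supply many of them: the Background cites a CP rehabilitation sample in which 56% had current or past IPV. Recruitment is province-wide and includes primary care, so there may be many centers; with 60 centers and 60% alignment at ICC 0.05, t-test error is only 6.7%. Women complete the questionnaire themselves, so staff do not rate outcomes. Each professional already holds a list of codes, and if those lists are center-specific, center may be recoverable.

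All of this stands as a limit on size. A reader might infer that p values will be too small for every hypothesised outcome. The documents do not support that: the inflation needs both within-center correlation and alignment, and it disappears without alignment. A reader might also infer that the k-fold split ignores center and that performance is therefore overstated. The article does not say how folds are formed, and a condensed article may leave that to the full plan. That part is a conditional consequence, not an error in the text.

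What the objection does not remove is that the tests named are independence tests, the sample size carries no design effect, and the listed variables stop at channel type.

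**Conclusion.** The point holds in conditional form. The stated t tests, ANOVA and sample size assume independent women, although recruitment and answering are by center and one type of center is defined by IPV. The direction of error is clear if the ICC is positive and IPV women come from different centers than CP-alone women. Its size ranges from negligible to a several-fold excess over 5%: about 8%–22% for the t test at ICC 0.05, 12–30 centers and 60%–100% alignment, and close to nominal at low ICC or weak alignment.

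Classifier optimism for new centers follows only if folds are random. In the milder layout checked it is modest at ICC 0.05 (AUC 0.53–0.58 where the truth is 0.50).

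The case for acting rests less on any one figure than on the low cost of recording center now and the impossibility of adding it later to anonymous records.

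**What to change.** 1. **Ethical Considerations (phase 2):** issue each center its own block of the participant codes already in use, so that center is known without identifying any woman. This should be settled before phase 2 codes are issued; organizations have already been contacted and the pilot is done.
2. **Data Analysis, group comparisons:** replace plain t tests and ANOVA by the same contrasts in a mixed model with a random intercept for center and small-sample degrees of freedom, or use cluster-robust errors. Put recruitment channel in the model as well, because a center effect does not remove confounding by channel. Where IPV status and center type coincide completely, no model can separate them, and the report should say so.
3. **Data Analysis, classifiers:** report performance with folds grouped by center, using as many folds as the number of centers holding each group allows. With 12 centers, one third of them IPV centers and full alignment, only 4 centers hold IPV women, so at most 4 folds could contain them.
4. **Sample Size Calculation:** state that the 90% power assumes independent women.

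The cost is a numbering rule and some wording. The downsides are wider intervals, lower and more variable classifier performance, and a center code held with anonymous records. Not reporting results by center limits the re-identification risk.

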#### Activity Patterns: Activity Patterns Scale

### Overview

The 3 activity patterns—pacing, avoidance, and persistence—can serve different goals and have varying impacts on health outcomes. To measure these patterns, we will use the Activity Patterns Scale [138]. This scale consists of 8 subscales, each with 3 items, for a total of 24 items. The subscales include pain avoidance, activity avoidance, task-contingent persistence, excessive persistence, pain-contingent persistence, pacing to increase activity levels, pacing to conserve energy for valued activities, and pacing to reduce pain. Participants will rate how well each statement applies to them on a 5-point scale ranging from 0=*not at all* to 4=*always*. Higher scores in a subscale indicate a stronger tendency to display the corresponding activity pattern. The instrument demonstrates adequate reliability as well as structural, convergent, and criteria validity. It has been specifically developed for use with the Spanish population [138].

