### Suicide Attempts and Thoughts: Ad Hoc Questionnaire

Participants will be asked whether they have ever considered committing suicide (yes or no); how frequently they have had such thoughts (never, rarely, sometimes, often, or always); and the number of suicide attempts, if any.

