### Medication Use and Illegal Drug Use: Ad Hoc Questionnaire

Participants will be asked to indicate the types of analgesics prescribed for their CP condition and their adherence to the prescribed medication regimen. They will be asked if they are taking the medication as prescribed, not taking it at all, or taking it in lesser or greater amounts. The questionnaire will also inquire about the use of nonprescribed medications and the consumption of other legal (eg, alcohol) and illegal drugs (eg, marijuana) for pain management. In addition, participants will be asked about other prescribed medications they may be taking and the purposes for which these medications are used.

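### The 90% power is calculated for a prevalence of pain avoidance that the plan never defines, while the only named tests compare means, so the stated power belongs to no named analysis

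*Protocol article*

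**What the plan says.** Three places in the protocol article bear on this point.

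- **Phase 2, Sample Size Calculation.** "To calculate the sample size, the prevalence of the pain-avoidance activity pattern was used". The other inputs are "the expected prevalence ratio assumed to be 2.0" between women exposed and not exposed to IPV, a prevalence of the pattern "within the study population, assuming it to be approximately 20" per cent, 30% exposed, alpha 5% and power 90%. The result is 359 women: 193 with CP alone, 83 with current IPV and 83 with past IPV.
- **Activity Patterns Scale, Overview.** Pain avoidance is one of eight subscales, with three items each scored 0 to 4. "Higher scores in a subscale indicate a stronger tendency to display the corresponding activity pattern". No threshold or classification rule is given.
- **Phase 2, Data Analysis.** The section speaks in general terms of hypothesis testing, estimation and prediction. The only inferential tests it names are two-tailed t "tests and ANOVA to compare means across groups". No test of proportions and no prevalence-ratio model is named.

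**The concern.** A power figure describes one test of one outcome. Here the outcome used for sizing is binary, the instrument yields a score, and the named tests compare means of scores. As written, the sized comparison cannot be run, because nothing says when a woman counts as having the pattern.

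Two things follow. First, a reader cannot tell what difference in the analysed quantity the study is able to detect. Second, if the prevalence comparison is later wanted, the cut-off would be a free choice on the one variable that justifies the sample size.

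There is a related question about the tests that are named. The group sizes are unequal by design, and t tests or ANOVA with a pooled variance lose control of the 5% level if the group variances differ as well.

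**Working it through.** **1. Reproduce the stated sample size.** Inputs from Sample Size Calculation: p0 = 0.20, p1 = 2.0 × 0.20 = 0.40, exposed-to-unexposed ratio r = 30/70 = 3/7, alpha 5%, power 90%. Two-sided testing is taken from Data Analysis.

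- Pooled proportion: 0.7 × 0.20 + 0.3 × 0.40 = 0.26.
- Uncorrected unexposed n = [1.960 √((1+r) × 0.26 × 0.74) + 1.282 √(r × 0.20 × 0.80 + 0.40 × 0.60)]² / (r × 0.20²) = (1.0275 + 0.7119)² / 0.01714 = 176.5.
- Continuity correction: (176.5/4) × [1 + √(1 + 2(1+r)/(176.5 × r × 0.20))]² = 192.8 unexposed; × 3/7 = 82.6 exposed.
- Rounded up: 193 and 83. A second exposed group of 83 gives 193 + 83 + 83 = 359, the stated figure.

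Reading 20% as the overall rate (15.4% vs 30.8%) gives 253 + 109, or 275 + 118 with the correction. Neither matches the stated groups. So the 90% belongs to a two-group comparison of proportions, 20% against 40%.

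**2. What the same groups give for a comparison of means.** The normal approximation to the standardised mean difference (SMD) detectable with 90% power is (1.960 + 1.282) × √(1/n1 + 1/n2).

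| Comparison | Normal approximation | Noncentral t | Rounded |
|---|---|---|---|
| 193 vs 83 | 0.425 | 0.427 | 0.43 |
| 83 vs 83 | 0.503 | 0.506 | 0.51 |

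The SMD is scale-free, so it does not matter that the article does not say whether subscale items are summed or averaged.

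If 20% vs 40% is assumed to come from cutting a normal score, the shift is z(0.80) − z(0.60) = 0.842 − 0.253 = 0.59 SD. A t test with 193 vs 83 then has about 99% power. The mismatch therefore does not point to a shortage.

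**3. Unequal groups and pooled variances.** The article gives no group SDs, so a range is assumed: IPV-group SD at 0.8, 1.25 and 1.5 times that of CP alone. For 193 vs 83, with k the SD ratio:

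- pooled variance = (192 + 82k²)/274
- squared SE used by the pooled t test = pooled variance × (1/193 + 1/83)
- true squared SE = 1/193 + k²/83
- type I error ≈ 2Φ(−1.96 × √(used/true))

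| k | Used | True | √(used/true) | Type I error |
|---|---|---|---|---|
| 0.8 | 0.01537 | 0.01289 | 1.092 | about 3% |
| 1.25 | 0.02013 | 0.02401 | 0.916 | about 7% |
| 1.5 | 0.02367 | 0.03229 | 0.856 | about 9% |

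Simulation with normal data at 193/83/83 gave the same 3%, 7% and 9% for the pooled t test and for ordinary ANOVA. The Welch t test and Welch ANOVA stayed near 5% throughout. With equal SDs and an SMD of 0.43, the Welch and pooled t tests both had about 90% power.

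**The case against.** The strongest reply is that this is a mismatch in documentation, not a design failure. N would not change, and a t test at these sizes is well powered. That stands, and nobody should read the point as saying the study is underpowered.

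It can also be said that the cut-off may exist elsewhere: the article cites a study in which 40.4% of patients with fibromyalgia showed the pattern, so some classification was used there, and an analysis plan not shown may carry it over. This softens the point but does not remove it. The article describes how the subscale is scored and which tests are used, and neither connects to the quantity that was sized.

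On variances, the article does not say that the tests are the pooled versions, and nothing in it shows that the IPV groups are more variable. In the opposite case the pooled tests are conservative, at about 3%. That is why a range is shown, and why the case for Welch rests on protection in either direction.

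Two stronger readings are tempting:

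- **That the categorical outcomes receive an invalid test.** Suicidal ideation is recorded yes/no, and medication adherence as "taking the medication as prescribed, not taking it at all, or taking it in lesser or greater amounts". But the article ties t tests and ANOVA to means and does not assign them to these outcomes. It names no test for them, and an analysis plan may. For yes/no outcomes, a t test at 193 vs 83 kept a simulated type I error of 4.7% to 5.2% for true rates of 5% to 40%.
- **That every test is run at an unadjusted 5%.** The article does not say so. Its 5% is the sample-size alpha, and it is silent on multiplicity, which may also sit in an analysis plan.

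**Conclusion.** The point holds in a limited form. The stated 90% power belongs to a continuity-corrected comparison of 20% with 40%; the article defines no binary outcome on which to run it and names no test that would. The 359 is reproduced exactly, so this conclusion rests on the document's own figures.

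No power shortage is shown. For means, the same groups give 90% power at an SMD of 0.43 (193 vs 83) and 0.51 (83 vs 83). The 99% figure at the latent equivalent depends on an assumed normal score.

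The variance point is conditional. Across assumed SD ratios of 0.8 to 1.5, the pooled tests' error runs from about 3% to 9% against a nominal 5%. The direction is unknown before data are seen. The documents do not support a claim of invalid tests for categorical outcomes or of unadjusted testing throughout.

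**What to change.** Keep N at 359 and make two changes of wording, ideally before any phase 2 data are seen; as of May 2025 the article reports recruitment only beginning.

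1. Tie the power to a named analysis, in one of two ways:
   - name the mean pain-avoidance subscale score as the sized comparison and restate the power as 90% for an SMD of 0.43 (193 vs 83) and 0.51 (83 vs 83); or
   - keep the prevalence as the sized quantity, state the rule that classifies a woman as showing the pattern, and name the prevalence ratio between groups as its analysis.
2. Specify Welch t tests and Welch ANOVA for comparisons of means.

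The cost is a few sentences. Welch tests give up almost no power when variances are equal, and no extra participants or measurements are needed.

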#### Variables and Instruments for Risk and Protective Factors

### Sociodemographic Characteristics

Age, belonging to a minority group (yes or no), years of education, annual household and personal incomes (categorized as €0 to €19,000; €20,000 to €40,000; and >€40,000; 1€=US $1.14), relationship status (single, partnered, or married), relationship duration (years), relationship satisfaction (10-point scale), CP diagnosis (yes or no), and time since CP diagnosis (years).

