Second, we aim to identify whether women with CP alone, those with CP and currently experiencing IPV, and those with CP and a past history of IPV present different profiles based on risk and protective factors for (disabling) CP and health outcomes. We hypothesize that women with CP and current or past experiences of IPV will show higher levels of disabling pain, more excessive persistence or avoidance activity patterns, lower levels of exercise, worse pain-related self-efficacy, greater pain worrying, informal social support that fosters dependence, lower levels of physical functioning, greater anxiety and depression, poorer medication management, increased illegal drug use, more suicidal thoughts and attempts, and a higher frequency of health system use. This hypothesis is based on previous findings indicating higher levels of disabling pain in women experiencing IPV compared to those with CP alone, as well as higher levels of suicidal thoughts, addiction issues, and greater use of health services compared to the general female population [23,165]. These characteristics will likely worsen in the presence of PTSD [82]. In addition, because pain-related self-efficacy and pain worrying have been linked to CP [65-69,78], we expect these factors to most effectively account for the profiles of women with a current or past history of IPV, along with informal social support, for the aforementioned reasons.

Moreover, because AI techniques go beyond traditional inferential statistics, it can identify patterns and relationships between variables that might remain undetected by the human eye. AI may uncover specific profiles within different groups of women, revealing how factors such as educational background, traditional feminine roles, ethnicity, and the duration of violence intersect with CP-related variables; for example, it could be that the pattern of excessive persistence is more common in women who are in the initial stages of the relationship and that they may seek to conform to traditional gender roles in an effort to meet their aggressors’ expectations. AI’s ability to process large datasets could lead to new insights and advances in understanding pain, its management, and its relationship with other concurrent psychosocial factors.

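### The phase 2 importance rankings have no no-association reference, and information gain and Gini favour long scales over yes/no items, so a raw rank cannot by itself confirm the hypothesis about leading factors

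*Protocol article*

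**What the plan says.** Aim 5 (Goals of This Study) is to find the factors that best explain the group profiles, provided that the groups differ. The phase 2 Data Analysis section gives the methods:

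- Feature ranking: "Methods such as information gain, gain ratio, Gini index, and relief will determine the importance of features". The ranking is meant to put the most influential factors for each group first.
- Model-based importance after the classifiers are fitted: "Feature importance evaluation will identify which variables most significantly influence" the predictions, combined with Shapley values and exploratory analysis.
- K-fold cross-validation, which is described for classifier performance, and t tests and ANOVA for group means.

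The Discussion (Summary) predicts the result. Of pain-related self-efficacy and pain worrying it says "we expect these factors to most effectively account for the profiles of women with a current or past history of IPV", and it adds informal social support.

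The candidate features differ widely in resolution. Some have two to four levels: "belonging to a minority group (yes or no"), income band, pain diagnosis, ever having considered suicide, general practitioner visits. Others are long scales: pain worrying 0-52, self-efficacy 22 items at 0-10 (0-220 in total), PTSD severity 0-63, and minutes of activity.

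**The concern.** Two features of the stated method matter.

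First, a ranking always has a top. If no feature were related to group, every one of these criteria would still put some feature first, and the article links no benchmark to the ranks that would show this. Cross-validation assesses how well a classifier predicts; it does not recalibrate the order of the features.

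Second, the order is not neutral. Information gain and Gini reduction grow by chance with the number of categories or possible cut points. A 53-point scale has many chances to split the groups well by luck, and a yes/no item has one. The same holds for random forest impurity importance, if that is the model importance used.

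At stake are the reading of aim 5, the test of the Discussion's hypothesis, and the assessment and intervention guidelines that the findings are to feed. A real difference in a yes/no factor could be listed below scales that carry no information.

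**Working it through.** **1. The planned sample, reproduced.** Inputs from Sample Size Calculation: "the expected prevalence ratio assumed to be 2.0"; prevalence of pain avoidance, "assuming it to be approximately 20" per cent (taken as the unexposed rate, so 40% in the exposed); IPV exposure "estimated at 30% based on findings from earlier research"; α 5% two-sided, power 90%.

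Ratio r = 0.30/0.70 = 0.4286. Pooled p = (0.20 + 0.4286 × 0.40)/1.4286 = 0.26.

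n₀ = [1.960·√((1 + 1/r) × 0.26 × 0.74) + 1.2816·√(0.20 × 0.80 + 0.40 × 0.60/r)]² / 0.20² = 176.5.

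Continuity correction: (176.5/4) × [1 + √(1 + 2(r + 1)/(176.5 × r × 0.20))]² = 192.8, so 193. The exposed group is 192.8 × 0.4286 = 82.6, so 83. Using 83 twice gives 193 + 83 + 83 = 359, as stated. The simulations use these group sizes, and 20% vs 40% is the planned effect.

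**2. Expected score with no association.** For a feature with k categories and three groups, 2N·ln2·IG is approximately chi-squared with 2(k − 1) degrees of freedom, so E(IG) ≈ (k − 1)/(N·ln2).

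- Yes/no item: 1/(359 × 0.693) = 0.004 (simulated 0.004).
- Scale cut at quartiles: 3/(359 × 0.693) = 0.012 (simulated about 0.012).

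For Gini, the group impurity is 1 − (0.538² + 2 × 0.231²) = 0.604, and E = (k − 1) × 0.604/358. For a yes/no item this is 0.0017 (simulated 0.0017).

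Simulated null means for the two hypothesised long scales:

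| Coding and score | Pain worrying | Self-efficacy | Yes/no |
|---|---|---|---|
| IG, raw values | 0.227 | 0.655 | 0.004 |
| IG, best split | 0.014 | 0.015 | 0.004 |
| Gini, best split | 0.0057 | 0.0062 | 0.0017 |
| Random forest impurity | 0.042 | 0.045 | about 0.007 |

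With best splits, a scale therefore starts at more than three times the score of a yes/no item (0.014/0.004 = 3.5; 0.0057/0.0017 = 3.4).

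**3. What leads with no association.** With 12 yes/no or few-level items and 12 scales, an unbiased ranking puts a scale first in 12/24 = 50% of runs. With best splits, a scale led in 90% (Gini) and 93% (information gain) in one simulation, and in about 95% in a second with different assumed distributions. With a fuller set of 33 features, four of them yes/no, a yes/no item led by information gain or Gini in 0-0.9% of runs under all three codings, against 4/33 = 12%.

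**4. A real yes/no difference among 12 noise scales.** Share of runs in which at least one noise scale ranked above it, by best-split Gini or information gain:

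- 20% vs 40% (planned size): 15% (Gini) and 22% (information gain) in one simulation, 13-25% in another.
- 10% vs 25%: 24% and 35% in one, 27-39% in another.

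Under random forest impurity importance the effect is far larger: at 20% vs 40%, on average 11.8 of the 12 noise scales ranked above the true factor (minimum 8).

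**5. Limits of the bias.**

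- With 33 null features, pain worrying or self-efficacy led in 0% (raw values), 4-7% (quartiles) and 12-15% (best split) of runs, against 2/33 = 6% by chance.
- A true 0.6 SD difference in anxiety led in 99% or more of runs by information gain or Gini, with quartiles or best splits.
- Gain ratio varied with coding. With raw values or best splits a yes/no item led in 0% of null runs; with quartiles yes/no items led in 38%, against 12% expected.

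**The case against.** A reader might infer that the method favours self-efficacy and pain worrying whatever the data show. The documents do not support that. Most rivals of these two are also many-valued scales (PTSD severity, anxiety and depression, the quality-of-life summaries, activity minutes), so the bias favours scales as a class. The hypothesis also includes informal social support. Real effects elsewhere usually still lead: among 33 features, a true yes/no difference of 20/40/40% ranked first in 80-97% of runs with quartile coding and 82-89% with best-split information gain or Gini.

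A reader might also infer that aim 5 rests on information gain, gain ratio and Gini alone and must yield a false answer when nothing differs. That goes too far. The plan also names relief, Shapley values and group tests, and makes aim 5 conditional on differences existing. Relief and Shapley values were not simulated. Gain ratio cannot be grouped with the other two, because its bias can reverse. The article does not say that its model importance is the impurity kind, so the random forest figures are conditional.

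Finally, coding and thresholds are details that a condensed article may leave to a fuller plan. That stands for the details, but not for the choice itself: the article commits to information gain and Gini as measures that decide importance, and their tilt towards many-valued features had the same direction under every coding tried. The t tests and ANOVA are not tied to the ranks in the text, and they compare means, which does not suit yes/no items.

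**Conclusion.** The point holds in a limited form. The stated rankings have no reference for no association, and information gain and Gini (with impurity importance, if used) under-rank yes/no and few-level factors relative to scales as a class. At 193/83/83 a scale leads in about 90-95% of null runs against 50% if unbiased, and a noise scale outranks a true yes/no difference of the planned size in roughly 13-25% of runs. Minority status and suicidal ideation are among the factors exposed to this. A high raw rank for self-efficacy, pain worrying or informal social support is therefore not, on its own, confirmation of the hypothesis.

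The size rests on assumed distributions and prevalences, independent features and 12 competing scales. The direction for information gain and Gini does not depend on the coding: the formulas in step 2 give it for categories and quartiles, and the best-split simulations agree.

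**What to change.** Keep the chosen scores but calibrate them.

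- Permute the group label across women, leaving each woman's features together, and recompute every score.
- Rank features by standardised excess over their own permutation distribution, or by permutation p value.
- Name a factor as explaining a profile only if it exceeds its null after Holm or false-discovery-rate control.
- Judge the Discussion's hypothesis on this calibrated ranking.

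The number of permutations must suit the correction. The smallest attainable p value with B permutations is 1/(B + 1). With 33 features, Holm's first threshold is 0.05/33 = 0.0015, so 500 permutations (1/501 = 0.0020) would be too few and at least 659 are needed.

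In a simulation with random forest importance and a true 10% vs 25% factor, calibration cut the mean number of the 12 noise scales ranked above it from 12.0 to 0.15; any noise scale outranked it in 6% of 34 runs, a small number of runs. The change needs analysis-plan wording and computing time, and no new data. The downside is that fewer factors may be named.
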